## Treatment Allocation

Treatment allocation and administration of medications will be performed by the study nurse or by the investigator at the clinic.

## Study Medications

The clinical trial material (CTM) to be evaluated in this study will be prepared and provided by Sigma-Tau i.f.r. S.p.A., Pomezia (Rome), Italy.

***Dihydroartemisinin (DHA) and Piperaquine (PPQ) = Artekin (Sigma-Tau)***

DHA-PPQ will be co-formulated as fixed-dose film tablets containing 20 mg or 40 mg of dihydroartemisinin and 160 mg or 320 mg of piperaquine.

***Artemether (A) and Lumefantrine (L) = Coartem (Novartis)***

AL will be co-formulated as fixed-dose film tablets containing 20 mg of artemether and 120 mg of lumefantrine.

The stability of the products used in the study will be determined in advance to assure suitability for use throughout the study. The results of this analyses will be included in the Trial Master File.

The CTM shall be stored in a secure area (e.g. pharmacy) until use.

## Packaging and Labelling

Each centre will receive a documented number of packages containing tablets of study drugs for the treatment of one subject (plus extra tablets for potential redosing, maximum 2 redosings). Each package will be identified by a label indicating at least the following information:

- Product name
- Trial reference
- Name and address of the Sponsor
- Batch number and expiry date
- Storage directions
- For clinical Trial only

## Dosage and Dosing Schedule

***Dihydroartemisinin (DHA, 20/40 mg) and Piperaquine (PPQ, 160/320 mg) = Artekin (Sigma-Tau)***

Medications will be administered as close as possible at the following times:

Day 0: hour “X”

Day 1: hour “X” + 24 hours

Day 2: hour “X” + 48 hours

The number of tablets will be based on bodyweight (see the relevant table in Appendix II).

***Artemether (A, 20 mg)) and Lumefantrine (L, 120 mg) = Coartem (Novartis)***

Medications will be administered at the following times:

Day 0: hour “X”

Day 0: hour “X” + 8 hours

Day 1: hour “X” + 24 hours

Day 1: hour “X” + 36 hours

Day 2: hour “X” + 48 hours

Day 2: hour “X” + 60 hours

The drug will be given at specific hours according to the manufacturer of Coartem. A glass of milk will be given to the child immediately after each administration of Coartem.

The number of tablets will be based on bodyweight.

## Drug Dispensing

The study medication will be administered at the clinic or at home by authorized members of the study team. Study medications given to infants and young children (<2 years old) will be crushed, mixed with water, and administered as a slurry if they are unable to swallow. Study medications administered to older children will be given as tablets or fractions of tablets to be taken orally with a glass of water. The study nurse or the investigator will directly observe the intake of study medications. Patients will be observed for one hour to ensure that the medications are not vomited or spat out. Any patient who vomits or otherwise expels the medication within 30 minutes of administration will be retreated with a second dose. If vomiting occurs between 30 and 60 minutes after treatment, only half of the original dose will be given.

# CONCOMITANT THERAPIES

## Disallowed Concomitant Drug Therapies

Any antimalarial, or antibiotic with antimalarial activity (erythromycin or other macrolides, co-trimoxazole or other sulfonamides, any tetracycline including doxycycline, and quinolones, clindamycin). Intake of these drugs leads to withdrawal of the patient from the further participation in the study.

## Allowed Concomitant Drug Therapies

During the trial patients can be prescribed drugs e.g. paracetamol, and antibiotics with no known antimalarial activity (penicillins, cephalosporins). The dose, route, time and duration of any concomitant medical treatment will recorded in the CRF.

## Special Conditions

Parents or guardians will be discouraged from obtaining drugs from any other source such as private pharmacies, markets or clinics. Parents/guardians will be encouraged to bring their children to the study clinic if their child is unwell or if they are worried about their child's health.

## Rescue Treatments

Patients with clinical treatment failure will be withdrawn from the study, treated, and followed up as per local practice. They will not have study investigations performed thereafter. Patients requiring rescue therapy (ETF, LCF) will be treated by members of the study team with quinine 10 mg/kg orally three times a day for 7 days or any other appropriate oral treatment unrelated to the study drugs. Any patient, who is diagnosed with severe malaria or danger signs during follow-up, will be referred for treatment with parenteral quinine and supportive measures at the local facility or hospital.

Patients with asymptomatic recurrent parasitaemia will also receive rescue therapy.

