## Primary Endpoint

The primary endpoint will be the PCR-corrected adequate clinical and parasitological response (PCR corrected ACPR) at D28.

ACPR is defined as the absence of parasitaemia on D28 irrespective of the axillary temperature without previously meeting any of the criteria of early treatment failure or late clinical or parasitological failure.

Patients with late asexual parasite reappearance will be considered ACPR if the PCR analysis shows a new infection rather than a recrudescence.

The total treatment failure is defined according to the WHO criteria (WHO 2003) as the sum of early* and late** treatment failures.

* Early Treatment Failure (ETF)

*(i) Development of danger signs or severe malaria on Day 0, Day 1, Day 2 or Day 3, in the presence of parasitaemia,*

*(ii) Parasite density on Day 2 > Day 0 count irrespective of axillary temperature,*

*(iii) Presence of parasitaemia on Day 3 with fever (axillary temperature ≥ 37.5°C),*

*(iv) Parasitaemia on Day 3 ≥ 25 % of count on Day 0.*

** Late treatment failure (LTF)

Late Clinical Failure (LCF)*:*

*(i) Development of danger signs or severe malaria after Day 3 in the presence of parasitaemia, (See Appendix V for the critera for severe malaria/danger signs)*

*(ii) Presence of parasitaemia and fever on any day from Day 4 to Day 28, without previously meeting the criteria of ETF.*

Late Parasitological Failure (LPF)*:*

*Reappearance of parasitaemia after initial clearance between day 4 and day 28 (identified as recrudescent infection by PCR analysis) in the absence of fever (axillary temperature <37.5°C) without previously meeting the criteria of ETF or LCF.*

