- Primary Analysis Populations = both the modified Intention To Treat (ITT) and the Per Protocol Populations.

With these assumptions, the sample size of 1500 patients (1000 in the Artekin group and 500 in the Coartem group) provides a power of approximately 83% for the lower bound of a 97.5 one-sided confidence interval for the treatment difference being above –0.05 in the modified ITT and 82% for the same analysis in the Per Protocol population (for the power calculation both continuity correction and inequality of variances under the null hypotheses have been considered).

For the historical comparisons, the clinical and statistical specifications for the sample size computations are as follows:

- Anticipated population proportion of clinical failures = as high as 10%.
- Confidence level = 95% (two-sided interval).
- Precision = 5 percentage points.
- Rate of patient attrition in the Per Protocol Population as compared to the ITT population (i.e. rate of withdrawals for any reason and protocol violations) = 30%.

According to Annex 4 of the WHO document “Assessment and Monitoring of Antimalarial Drug Efficacy for the Treatment of Uncomplicated Falciparum Malaria – 2003”, a sample size of at least 200 patients would be required in each treatment group for estimating the proportion of clinical failures to within a 5 percentage point of the true value with 95% confidence.

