# PATIENT WITHDRAWAL CRITERIA

During the study, the following conditions are reasons **for stopping the study treatment and/or for excluding the patients from further efficacy assessments:**

1. Any treatment failure (including early failures);

2. Withdrawal of informed consent;

3. Use of antimalarial drugs (or antibiotics with antimalarial activity) outside of the study protocol;

4. Persistent vomiting of study drugs **on Day 0**  (at least twice the same dose);

5. Failure to complete the study treatment

6. Investigator's request for safety reasons (for example, onset of serious adverse events, necessitating study interruption);

6. Lost to follow-up (unable to locate the patient) before Day 28.

Patients with one or more of the conditions listed above will have to be followed-up for the safety assessment until Day 42

These reasons for premature withdrawing will be referred to Day 28 (primary evaluation time).

The reasons for withdrawing between Day 29 and Day 42 will also be recorded in the study CRF.

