# SAFETY VARIABLES

Safety and tolerability of the treatments will be evaluated by recording Adverse Events (AEs) and grading, laboratory, ECG and vital signs evaluations.

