## Adverse Events

At each visit, the Investigator will ascertain the occurrence of any adverse events since the last visit. Any event must be recorded on the CRF.

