### Defintion of a serious adverse event

A serious adverse event (experience) (SAE) or reaction is any untoward medical occurrence that at any dose :

- results in death;
- is life-threatening;
- requires hospitalization (other than for drug administration) or prolongation of existing hospitalization;
- results in persistent or significant disability/incapacity; or
- is a congenital anomaly/birth defect.

And also

- other important medical events (jeopardise the subject or require intervention to prevent one of the other outcomes listed in the definition above).

**All serious adverse events, whether or not deemed drug-related, or expected, must be reported immediately or within 24 hours (one working day), using the Serious Adverse Event Notification Form , by telefax to :**

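### Section 4.4 stops study investigations after clinical treatment failure, while section 5 requires safety follow-up to Day 42; both rules cannot be followed for the same child

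*Combined protocol and SAP*

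**What the plan says.** Protocol section 4.4 (Rescue Treatments) states: "Patients with clinical treatment failure will be withdrawn from the study, treated, and followed up as per local practice". The next sentence is: "They will not have study investigations performed thereafter". Clinical failure is naturally read as early treatment failure (ETF) and late clinical failure (LCF), although those labels are attached to the following sentence, on rescue therapy. Children with symptom-free recurrence also receive rescue treatment, but 4.4 states no stop for them.

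Section 5 (Patient Withdrawal Criteria) puts any treatment failure first in its list. It describes the listed conditions as grounds for ending study treatment and/or efficacy assessment, and says that children with any of them "will have to be followed-up for the safety assessment until Day 42".

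Section 7 gives the content of safety assessment: "Safety and tolerability of the treatments will be evaluated by recording Adverse Events (AEs) and grading, laboratory, ECG and vital signs evaluations". Section 3.5 gives every child 42 days of follow-up. Section 9.4 includes every dosed child in the safety analysis, and section 2.2 makes the comparison of safety profiles a secondary objective.

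Section 9.2.1 requires a child diagnosed as re-infected to be taken off follow-up on that day. It does not say whether this means efficacy follow-up only.

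**The concern.** A child with ETF or LCF falls under 4.4 and section 5 together. One rule ends study investigations; the other requires the assessments that section 7 lists. Nothing in the document says which prevails, so sites may act differently.

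If 4.4 is followed, the remaining vital signs, scheduled laboratory tests and, for early failures, the Day 7 ECG stop at a moment set by the outcome of treatment. Non-serious adverse events may stop as well, because section 7.1 ties their collection to visits: "At each visit, the Investigator will ascertain the occurrence of any adverse events since the last visit". Section 3.4.1 justifies the 2:1 allocation partly by a larger DHA+PPQ safety database, and this would thin that database selectively. Section 1.3 names piperaquine and lumefantrine as the partner drugs with the longer half-life, so observation after an early failure still bears on study drug.

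**Working it through.** The plan gives no figure on this point. The check sets the rules side by side and then counts what each failure day would cost.

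**1. The rules**

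| | Section 4.4 | Section 5 | Section 9.2.1 |
|---|---|---|---|
| Who | Clinical treatment failure | Any treatment failure | Re-infected children |
| What ends | Study participation and study investigations | Study treatment and/or efficacy assessment | Follow-up, type not stated |
| What continues | Local practice | Safety assessment to Day 42 | Not stated |

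ETF and LCF fall under the first two columns at once. Section 3.8 has filter-paper samples from late failures genotyped afterwards, so a site cannot know on the day whether a recurrence is a re-infection. The 9.2.1 rule therefore bears on every recurrence, with or without fever.

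**2. Loss per child if 4.4 is followed**

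Inputs from the follow-up chart (section 3.6): visits on Days 0, 1, 2, 3, 7, 14, 21, 28, 35 and 42; unconditional laboratory tests on Days 0, 3, 28 and 42; unconditional ECGs on Days 0, 2 and 7. The chart makes later ECGs conditional on an earlier abnormal one. Days lost = 42 − failure day.

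| Failure on | Days lost | Visits lost | Laboratory time points lost | Unconditional ECGs lost |
|---|---|---|---|---|
| Day 1 | 42 − 1 = 41 | 8 | 3 (Days 3, 28, 42) | 2 (Days 2, 7) |
| Day 2 | 42 − 2 = 40 | 7 | 3 (Days 3, 28, 42) | 1 (Day 7) |
| Day 3 | 42 − 3 = 39 | 6 | 2 (Days 28, 42) | 1 (Day 7) |
| Day 14 | 42 − 14 = 28 | 4 | 2 (Days 28, 42) | 0 |
| Day 28 | 42 − 28 = 14 | 2 | 1 (Day 42) | 0 |

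Section 3.2 allows failure this early. Danger signs with parasitaemia count from Day 0, and a Day 2 criterion is "Parasite density on Day 2 > Day 0 count irrespective of axillary temperature".

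**3. Children affected**

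The plan does not state a rate of ETF plus LCF. Per 1%: 1500 × 0.01 = 15 children, of whom 1000 × 0.01 = 10 are on DHA+PPQ and 500 × 0.01 = 5 on A+L.

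**4. Share of safety observation lost in an arm**

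With failure rate f and mean failure day d, share lost = f × (42 − d)/42. The rates and days here are assumptions for illustration.

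- f = 1%, d = 14: 0.01 × 28/42 = 0.67%.
- f = 1%, d = 28: 0.01 × 14/42 = 0.33%.
- f = 10%, d = 14: 6.7%; f = 10%, d = 28: 3.3%.

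The first two lines have equal failure rates and unequal losses. Arms can therefore differ in observation time through failure rates or through failure timing.

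**5. What limits the loss**

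The chart's column for the day of recurrent parasitaemia has examination, vital signs, ECG, haematology and adverse event recording, but no clinical chemistry. The section 3.8 text on unscheduled visits adds haemoglobin at failure. For other tests it refers back to visits 5 to 7, where laboratory tests on Days 7 and 14 depend on an earlier abnormality, so chemistry at failure is not assured. Serious events are reported without exception for failures: "All serious adverse events, whether or not deemed drug-related, or expected, must be reported immediately or within 24 hours".

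**The case against.** The strongest reply is that the texts can be read together: 4.4 ends tests, and section 5 keeps only adverse event and outcome follow-up. In support, the section 5 sentence also covers withdrawn consent and loss to follow-up, where scheduled tests cannot be done, so it cannot mean the full set of assessments for everyone listed. The study team also gives the rescue treatment, and section 4.3 encourages return to the study clinic. On this reading the missing tests are intended.

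Part of this stands. The section 5 duty needs a limit for children without consent or contact. The reading still does not fit section 4.4, which withdraws the child and leaves follow-up to local practice, or section 7, which defines safety evaluation by tests as well as events. A child with clinical failure is known and being treated, so nothing about the situation prevents assessment. Which text to change is a judgement, and the sponsor could narrow section 5 instead. Section 5 is the dedicated withdrawal section and agrees with sections 3.5 and 9.4, which favours changing 4.4.

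It is also fair that data after failure are partly confounded by rescue therapy, for example 7 days of quinine, and that vital signs and ECG are analysed only descriptively.

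A reader might infer that about 150 children are affected, from the section 3.4.1 input "Anticipated population proportion of clinical failures = as high as 10" per cent (1500 × 0.10 = 150). The document does not support that. The figure is a precision input for the historical comparison. Total failure under section 3.2 includes symptom-free recurrences, while febrile re-infections can meet the LCF definition before PCR. The true number could be lower or higher.

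**Conclusion.** The conflict is real and should be corrected. Sections 4.4 and 5 give incompatible instructions for ETF and LCF, and 9.2.1 leaves it unclear whether re-infected children continue safety follow-up. If 4.4 is followed, each affected child loses between 14 days (failure on Day 28) and 41 days (failure on Day 1) of planned safety observation, with the visits and tests counted above. Each 1% of clinical failure affects 15 children. This assumes that sites apply 4.4 literally and that the chart is otherwise kept.

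Three stronger conclusions are not supported.

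- Bias in the primary result: these children have already met a failure criterion or are resolved by PCR, so the Day 28 endpoint and the stated power do not depend on later safety visits.
- Certain imbalance between arms: this needs a difference in failure rates or failure timing, and the plan states neither.
- Loss of all safety information: failure-day assessments and serious event reporting remain.

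Nor can symptom-free recurrence be treated as free of the problem merely because 4.4 states no stop there, given 9.2.1.

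**What to change.** In section 4.4, replace the withdrawal wording and the sentence on study investigations with: *Treatment failure ends efficacy assessments only; AE recording, vital signs, scheduled safety laboratory tests and any indicated ECG continue to Day 42 in both arms, as section 5 requires, where consent and contact remain.*

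In section 9.2.1, state that termination means efficacy follow-up only, so that all children with recurrent parasitaemia follow one rule.

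Record the rescue drug and its start date in the CRF as a concomitant treatment, so that events before and after rescue can be separated. Section 4.2 already largely covers this.

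The cost is a wording amendment, which section 14.4 requires the ethics committee to approve before it takes effect. Visits and blood draws already in the follow-up chart (about 2 ml per laboratory draw, section 7.2) would continue in children on rescue therapy, and the resulting data would be partly confounded by that therapy. If the sponsor intended adverse event follow-up only, this is more than it had in mind; it should then narrow section 5 and say so.

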# PATIENT WITHDRAWAL CRITERIA

During the study, the following conditions are reasons **for stopping the study treatment and/or for excluding the patients from further efficacy assessments:**

1. Any treatment failure (including early failures);

2. Withdrawal of informed consent;

3. Use of antimalarial drugs (or antibiotics with antimalarial activity) outside of the study protocol;

4. Persistent vomiting of study drugs **on Day 0**  (at least twice the same dose);

5. Failure to complete the study treatment

6. Investigator's request for safety reasons (for example, onset of serious adverse events, necessitating study interruption);

6. Lost to follow-up (unable to locate the patient) before Day 28.

Patients with one or more of the conditions listed above will have to be followed-up for the safety assessment until Day 42

These reasons for premature withdrawing will be referred to Day 28 (primary evaluation time).

The reasons for withdrawing between Day 29 and Day 42 will also be recorded in the study CRF.

# PROTOCOL VIOLATIONS

A protocol violation occurs when an event happens that does not allow for accurate interpretation of response to treatment.

Patients meeting one of the following criteria will be considered protocol violations but will not be withdrawn from follow-up:

- **violation of any eligibility criteria;**
- PCR unclassifiable results;
- failure to attend a follow-up visit on Days 0-2 and patient cannot be located within 6 hours of scheduled time;
- failure to attend two consecutive follow-up visits from Day 3 to Day 28 (visits from Day 3 to 28 must take place within 24 hours of the scheduled time).

**The violations listed above are not valid reasons for withdrawing the patients from follow-up (both efficacy and safety assessments). On the contrary, the Investigator must do his/her best to respect the allowed time windows at every visit, even if a violation occurred at a previous visit (i.e. a previous visit did not take place or occurred outside the allowed time window).**

**The protocol violations listed above will not be taken into account for establishing patient inclusion in the Intention-To-Treat population while they will be a reason for excluding the patients from the Evaluable population**.

# SAFETY VARIABLES

Safety and tolerability of the treatments will be evaluated by recording Adverse Events (AEs) and grading, laboratory, ECG and vital signs evaluations.

## Adverse Events

At each visit, the Investigator will ascertain the occurrence of any adverse events since the last visit. Any event must be recorded on the CRF.

### Definition of an adverse event

An AE is any untoward medical occurrence in a patient or clinical investigation subject administered a pharmaceutical product and which does not necessarily have a causal relationship with this treatment.

An AE can therefore be any unfavourable and unintended sign (that could include a clinically significant abnormal laboratory finding), symptom or disease temporally associated with the use of a medicinal product, whether or not considered related to the medicinal product.

### Severity, relationship of event to study drug, and outcome

The severity of a clinical adverse event is to be scored according to the following scale :

1 Mild Awareness of sign or symptom, but easily tolerated

2 Moderate Discomfort enough to cause interference with usual activity

3 Severe Incapacitating with inability to work or perform usual activity

The relationship of an adverse event to study drug is to be assessed according to the following definitions :

1 Definitely unrelated

Should be reserved for those events which occur prior to test drug administration (e.g., washout or single-blind placebo) or for those events which cannot be even remotely related to study participation (e.g. injury caused by a third party).

2 Unlikely

There is no reasonable temporal association between the study drug and the suspected event and the event could have been produced by the subject's clinical state or other modes of therapy administered to the subject.

3 Possible

The suspected adverse event may or may not follow a reasonable temporal sequence from study drug administration but seems to be the type of reaction that cannot be dismissed as unlikely. The event could have been produced or mimicked by the subject's clinical state or by other modes of therapy concomitantly administered to the subject.

4 Probable

The suspected adverse event follows a reasonable temporal sequence from study drug administration, abates upon discontinuation of the drug, and cannot be reasonably explained by the known characteristics of the subject's clinical state.

5 Definitely related

Should be reserved for those events which have no uncertainty in their relationship to test drug administration: this means that a rechallenge was positive.

The outcome of each AE must be assessed according to the following classification:

| - completely recovered : | The patient has fully recovered with no observable residual effects |
| --- | --- |
| - not yet completely recovered : | Improvement in the patient’s condition has occurred, but the patient still has some residual effects |
| - deterioration : | The patient’s overall condition has worsened |
| - permanent damage : | The AE has resulted in a permanent impairment |
| - death : | The patient died due to the AE |
| - ongoing : | The AE has not resolved and remains the same as at onset |
| - unknown : | The outcome of the AE is not known because the patient did not return for follow-up (lost to follow-up) |

